**4.5 Follow up Procedures**

At the end of the study participants randomised to the usual care group will be given an opportunity to ask questions and receive information.

**4.6 End of Study Definition**

Once the primary outcome variables have been appropriately assessed and data analysis completed, this marks the end of the study.

### 5. Laboratories

All blood samples will be analysed in the Viapath laboratory using quality assured procedures.

**5.1 Central/Local Laboratories**

Blood Samples will be collected locally and sent to the Viapath lab.

**5.2 Sample Collection/Labelling/Logging**

Blood samples will be tracked and identifiable by the unique patient code. Sample results will be entered onto the patient record.

**5.3 Sample analysis procedure**

The sample analysis will be done through Viapath

**5.4 Sample storage procedure**

Sample will be destroyed

**5.5 Data Recording/Reporting**

The study will be written up as a thesis for a Doctorate Degree. The results will be reported in peer reviewed scientific journals, presented at relevant conferences as a poster or presentations such as Diabetes UK conference, Foundation of European Nurses (FEND) conference, Diabetes, Hypertension, Metabolic Syndrome and Pregnancy symposium (DIP), and others.

We will convene a patient seminar at the end of the study inviting all participants and other patient organisations to attend and provide comment and feedback on the study findings

### 6. Assessment of Safety

We have carefully considered the potential clinical hazards associated with this study. These have been discussed by clinical colleagues not directly involved in the study. There are no major risks involved with participation in this study. The study will have in place the following safety monitoring procedures: an incident log for every patient to record any adverse events; an incident log for all clinical research areas to monitor adherence to study protocol and SOP and for recording any incidents that may occur in the conduct of the study; weekly team meetings to consider any difficulties or potential hazards; and clear line of reporting for any adverse events. All team members have completed the KHP Good Clinical Practice. The clinical team will be advised of the patient’s participation in the study to ensure no contradicting intervention during the study.

The responsibility for the conduct of the study resides with all team members with overall responsibility resting with the Chief Investigator (CI). In addition to the weekly team meetings a monthly trial monitoring committee will be held for the duration of the study. This committee is comprised of: the CI, motivational interviewer, 1 diabetes consultant psychiatrist, 1 diabetes medical consultant, 1 diabetes nurse consultant, 2 researchers, a patient representative and a representative from the CTU.

Ethical issues around provision of information to the usual care group will be addressed by providing patients in this group with information about diabetes and healthy lifestyles after completion of follow-up measurements.

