| Up to first year of life | 1-2 as per early post-partum | 1-3 as per pregnancy +   1. Daily calorie target = 1,200 (+400 if breast feeding). | ≥5% weight loss from 2 months post-partum. |
| *= Cedergren, M. (2007) Optimal gestational weight gain for body mass index categories. Obstet Gynecol. 2007 Oct;110(4):759-64. | | | |

The intervention is comprised of 5 face to face interactions (60 minutes) across the antenatal and postpartum periods delivered using motivational interviewing (MI) techniques. The focus of the sessions are targeted to reflect the changing context of needs during pregnancy and the postpartum period. The intervention is supported by a facilitated ‘WhatsApp’ group, motivational text messages, a pedometer and a website. An overview of the GODDESS intervention is provided in figure 1.

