**Face-face MI session 4 (6 months postpartum)**

**Face-face MI session 3 (3 months postpartum)**

**DROP OUT**

Pre-collected data used if agreed

**Interim data visit (3 months postpartum):** Questionnaires; anthropometry; blood pressure; blood sample; OGTT; provided with 7 day accelerometer

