**Face-face MI session 2 (33-37 weeks’ gestation)**

**CONTROL GROUP:**

Routine care

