**9.2 Case Report Form (CRF)**

Each participant within this study will be assessed to ensure that they have undergone all appropriate procedure and to monitor patient safety throughout the course of the study. The CRF incorporates the following:

- Eligibility/exclusion criteria checklist include: Demographic and biometric data, Insulin data, weight and BMI; and diabetes complications, history of DKA, current medicines and past-medical history (from the medical record).
- Blood test results (fasting blood glucose, HbA1c)
- weight, height, BMI, waist circumference
- Visit details
- Adverse events, withdrawal from study, SAE form
- Study questionnaires include: Multiple pass 24 hour diet recall, Beacke physical activity questionnaire, Risk Perception Survey for Developing Diabetes, Hospital anxiety and depression scale

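### No visit schedule includes an adverse-event enquiry, and the intervention arm alone has extra staff contact, so any table of logged events by arm is open to ascertainment bias

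*Protocol*

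**What the plan says.** Section 6 (Assessment of Safety) provides "an incident log for every patient to record any adverse events", with weekly team meetings, a monthly monitoring committee and a line of reporting. Section 9.2 says the CRF serves "to monitor patient safety throughout the course of the study" and lists among its contents "Adverse events, withdrawal from study, SAE form". Appendix 1 sets deadlines for reporting a serious event once it is known.

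No section says who asks about events, when, or over what recall period. The flowchart in Section 2.3 describes the 3-month data visit as "Questionnaires; anthropometry; blood pressure; blood sample; OGTT; provided with 7 day accelerometer", and the 9-month visit in the same terms. The schedule table in Section 2.3 has no adverse-event row. The lists for data collection visits 1 to 3 in Section 4.2 have no such item, and neither do the topics of the 9-month interview.

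On contact, Section 2.2 states: "The intervention is comprised of 5 face to face interactions (60 minutes) across the antenatal and postpartum periods". It adds: "The intervention is supported by a facilitated ‘WhatsApp’ group, motivational text messages, a pedometer and a website". The control arm has routine care and the data visits.

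**The concern.** A log records only what staff come to hear. If nobody is scheduled to ask, what is heard depends on how often, and how openly, staff talk with each woman. Here that differs by arm in a trial that Section 4.3 says cannot be double-blind.

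The intervention changes diet, activity and weight during pregnancy and after birth, and the trial is meant to precede a larger one. Whoever plans that trial will probably look at the events by arm. An excess in the intervention arm could come from contact alone, and a real excess could be put down to contact. No later analysis can recover minor events that control women were never asked about, so the place to deal with this is the protocol's data collection.

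**Working it through.** **1. Is an enquiry scheduled anywhere?** I compared the places where it could stand.

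- Flowchart, Section 2.3: contents of the baseline, 3-month and 9-month visits. No adverse-event item.
- Schedule table, Section 2.3: no adverse-event row.
- Visit lists and interview topics, Section 4.2: no adverse-event item.
- CRF, Section 9.2: a form exists but is not tied to a visit.
- Section 6 and Appendix 1: logging and reporting, not how events are elicited.

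**2. Contacts after baseline.** The baseline visit cannot capture an event that happens after randomisation, so it is left out.

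- Both arms: data visits at 3 and 9 months. Sessions 3 and 5 fall at the same times.
- Intervention only: "Face-face MI session 2 (33-37 weeks’ gestation") and "Face-face MI session 4 (6 months postpartum"), plus WhatsApp and text messages.

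The face-to-face time points are 4 against 2. The content differs as well. Section 4.4 has session 2 draw out worries and what has gone less well, and session 3 go over the birth. It also places a review of pregnancy outcomes before session 3 in the intervention schedule only.

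**3. What this could do to a by-arm table.** The protocol gives no capture rate, so this step is illustrative. Assume equal true risk in both arms, and that each face-to-face contact after an event brings it to notice with the same probability q. With k contacts remaining, capture = 1 − (1 − q)^k. The value of k depends on when the event occurs:

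| Event occurs between | k, intervention | k, control | Ratio, q=0.1 | q=0.5 | q=0.8 | q=1 |
|---|---|---|---|---|---|---|
| baseline and session 2 | 4 | 2 | 1.81 | 1.25 | 1.04 | 1.00 |
| session 2 and 3 months | 3 | 2 | 1.43 | 1.17 | 1.03 | 1.00 |
| 3 and 6 months | 2 | 1 | 1.90 | 1.50 | 1.20 | 1.00 |
| 6 and 9 months | 1 | 1 | 1.00 | 1.00 | 1.00 | 1.00 |

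First row at q = 0.1: 1 − 0.9^4 = 0.344 and 1 − 0.9^2 = 0.190, so 34% against 19%, ratio 1.81. Third row at q = 0.5: 1 − 0.5^2 = 0.75 and 1 − 0.5 = 0.50, ratio 1.50.

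The model leaves out WhatsApp and the open conversation at sessions 3 and 5, which could raise capture in the intervention arm. It also leaves out medical records, which would bring the ratio towards 1 for events recorded there.

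**4. With the fix.** If both arms are asked the same question at 3 and 9 months and only those answers are tabulated, k is equal in every row. The ratio is then 1.00 for any q, provided q is the same in both arms.

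**The case against.** Four points on the other side deserve weight.

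- **No comparison of harms is planned.** Section 2.4 lists adverse events under neither the primary nor the secondary outcomes. The analysis text covers feasibility and preliminary efficacy, and no safety progression rule appears. This stands. A reader might infer that a planned comparison is biased, but the protocol contains no such comparison. The point applies only to a by-arm table that someone may draw from the log.
- **Passive logging is an inference.** A reader might conclude that events are recorded only as they come to notice. The protocol is silent on the method; it does not say this. A prompt may sit in the CRF or in an operating procedure that is not shown. But the schedule table and visit lists itemise each questionnaire and measurement and leave this one out, so staff who follow them have no instruction to ask.
- **Controls are not out of reach.** A reader might infer that they have no contact from baseline to 3 months postpartum. They have no scheduled study visit, but routine care continues, the clinical team knows of their participation (Section 6), and the research team may read their records (Section 9.3). Birth outcome data are also collected (Section 2.4). Hospital and birth events can therefore be found in both arms. This stands, and it confines the problem mainly to minor events.
- **The contact excess is smaller than it looks.** Counting five intervention contacts against three for controls includes baseline, which cannot capture later events. Three of the five sessions also fall at data-visit times, so the face-to-face excess is two time points plus remote contact.

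What remains is that the schedule fixes no common enquiry and that contact is unequal by design.

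**Conclusion.** The point holds in a limited form. The protocol promises a record of any adverse event for every patient but schedules no enquiry in either arm, while one arm has more contact, and more open contact, with staff. Any by-arm tabulation of logged events is therefore open to ascertainment bias, chiefly for minor events absent from medical records.

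The size cannot be stated. Under the assumed equal capture per contact, the ratio with no true difference lies between 1.00 and 1.90 for q from 1 down to 0.1, depending on when the event occurs. It is near 1 where capture is nearly complete, as it may be for serious events found in records. The documents do not support saying that the trial's results are biased or that a go/no-go decision on safety is compromised. This is an inexpensive improvement in data collection for a 60-woman feasibility trial.

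**What to change.** 1. Add an adverse-event row to the schedule table in Section 2.3 and an item to the lists for data visits 2 and 3 in Section 4.2. Use the same question and the same recall period for both arms.
2. State that hospital and birth events are extracted for both arms, in the same way, from the medical records the team already accesses.
3. State that any tabulation of events by arm uses only these common sources. Events first learned of at MI sessions or through WhatsApp are still logged and reported for safety as now, but are listed separately.

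The cost is one extra question at each of two existing visits, one further item in the record extraction, and a sentence on tabulation. The downside is some recall loss for minor events. Visits, treatment and safety reporting deadlines do not change.

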**6.1 Ethics Reporting**

We do not consider that there are any major ethical dilemmas in relation to this study. All patients will give fully informed written consent for their participation, which will be gained from an appropriately trained medical professional. The study will proceed subject to NHS Research Ethics Committee approval and Health Research Authority approval. The study will be indemnified by the no-fault insurance policy of King’s College London.

### 7. Trial Steering Committee

We will have a study committee comprised of: the CI, PIs, 1 diabetes consultant psychiatrist, 1 diabetes nurse consultant, 1 researcher and a patient representative.

### 8. Ethics & Regulatory Approvals

The study will be reviewed by ……..Ethics

### 9. Data Handling

**9.1 Confidentiality**

Eligibility Checklist Forms and the Participant Information and signed Consent Forms will be printed, signed and dated by the research team and a copy will be returned to the participant and another copy to the hospital medical notes.

The printed forms will be stored within a secure lockable file location at King’s College London. In addition, a copy of each of these forms for each participant are stored electronically within King’s College’s secure research database.

All participants recruited to the study are recorded and tracked on the King’s college secure research project database. Participant tracking records include the participant’s personal details, when their eligibility and consent forms were received. These participant tracking records then form the base for participant tracking throughout the study, which highlights the allocated ID number for participants and the study visits and follow up dates for the duration of the study.

Participants will be reassured that the information they provide will be confidential. We will also ensure it is not possible to identify participants from our publically available research reports.

**9.2 Case Report Form (CRF)**

Each participant within this study will be assessed to ensure that they have undergone all appropriate procedure and to monitor patient safety throughout the course of the study. The CRF incorporates the following:

- Eligibility/exclusion criteria checklist include: Demographic and biometric data, Insulin data, weight and BMI; and diabetes complications, history of DKA, current medicines and past-medical history (from the medical record).
- Blood test results (fasting blood glucose, HbA1c)
- weight, height, BMI, waist circumference
- Visit details
- Adverse events, withdrawal from study, SAE form
- Study questionnaires include: Multiple pass 24 hour diet recall, Beacke physical activity questionnaire, Risk Perception Survey for Developing Diabetes, Hospital anxiety and depression scale

**9.3 Record Retention and Archiving**

The Chief Investigator (CI) and the research team will have access to participants' personal data during the study. Participants will be informed, both verbally and through a Patient Information Sheet, that the CI and the research team will access their medical records during the study, in order to record their clinical information. Participants will sign an Informed Consent to confirm their willingness for the research team to access their personal information*.*

Data files will be stored on a password protected computer at the researcher’s University. Paper questionnaires will be stored in a locked filing cabinet in a research office at King's College London (KCL). This data will be primarily analysed by the PhD student with discussion of the analysis with academic supervisors and members of the research team throughout. Support from a statistician will be sought in case of need. Data analysis will be carried out in KCL, using SPSS on a password protected university computer.

Each participant will be assigned a unique study identifier and all data will be coded with that study identifier. Personalised information with the unique study identifier will be managed securely in restricted access, lockable containers at King’s College London (KCL).

No personalised data will be stored electronically, all data will be anonymised and any electronic data will be stored on a password protected university computers. The data held on these computers will not be identifiable back to personalised data.

Following completion of the study the personal data will be stored locally and accessed for 6-12 months after the study has ended. The electronic data generated by the study will be stored electronically on a university computer at King’s College London for 5 years. It will not contain any participant identifiable data and will only be used if there are any queries regarding the study after publication and future study design.

**9.4 Compliance**

The CI will ensure that the trial is conducted in compliance with the principles of the Declaration of Helsinki (1996), and in accordance with all applicable regulatory requirements including but not limited to the Research Governance Framework, Trust and Research Office policies and procedures and any subsequent amendments*.*

**9.5 Clinical Governance Issues**

The sponsor will determine the appropriate level and nature of monitoring required for the trial.  Risk will be assessed on an ongoing basis and adjustments made accordingly. The degree of monitoring will be proportionate to the risks associated with the trial. A trial specific oversight and monitoring plan will be established for studies. The trial will be monitored in accordance with the agreed plan

**9.6 Non-Compliance**

The sponsor will maintain a log of the non-compliances to ascertain if there are any trends developing which to be escalated. The sponsor will assess the non-compliances and action a timeframe in which they need to be dealt with. Each action will be given a different timeframe dependant on the severity. If the actions are not dealt with accordingly, the R&D Office will agree an appropriate action, including an on-site audit.

### 10. Finance and Publication Policy

**Amount: £241,208**

**Source of funding:** student bench fees from student sponsorship managed by KCL and KCH.

Name and address of funder

**Name:** NIHR Trainees Coordinating Centre

**Address:** [name]

**[contact]

**Email:** [[contact]](mailto:[contact])

The trial will be registered on the ClinicalTrials.org. Part of the research will be written up as a thesis for a doctorate at King’s College London. The results will be disseminated locally, nationally and internationally in meetings and conferences for healthcare professionals. Papers will be published in health journals associated with diabetes and newsletters for people with diabetes.

**Appendix 1 – Information with regards to Safety Reporting in Non-CTIMP Research**

|  | **Who** | **When** | **How** | **To Whom** |
| --- | --- | --- | --- | --- |
| **SAE** | Chief Investigator | -Report to Sponsor within 24 hours of learning of the event  -Report to the MREC within 15 days of learning of the event | SAE Report form for Non-CTIMPs, available from NRES website. | Sponsor and MREC |
| **Urgent Safety Measures** | Chief Investigator | Contact the Sponsor and MREC Immediately  Within 3 days | By phone  Substantial amendment form giving notice in writing setting out the reasons for the urgent safety measures and the plan for future action. | Main REC and Sponsor  Main REC with a copy also sent to the sponsor. The MREC will acknowledge this within 30 days of receipt. |
| **Progress Reports** | Chief Investigator | Annually ( starting 12 months after the date of favourable opinion) | Annual Progress Report Form (non-CTIMPs) available from the NRES website | Main REC |
| **Declaration of the conclusion or early termination of the study** | Chief Investigator | Within 90 days (conclusion)  Within 15 days (early termination)  *The end of study should be defined in the protocol* | End of Study Declaration form available from the NRES website | Main REC with a copy to be sent to the sponsor |
| **Summary of final Report** | Chief Investigator | Within one year of conclusion of the Research | No Standard Format  However, the following Information should be included:-  Where the study has met its objectives, the main findings and arrangements for publication or dissemination including feedback to participants | Main REC with a copy to be sent to the sponsor |

